## Abstract

**Background:**

Alcohol causes huge problems for population health and for society, which require interventions with individuals as well as populations to prevent and reduce harms. Brief interventions can be effective and increasingly take advantage of the internet to reach high-risk groups such as students. The research literature on the effectiveness of online interventions is developing rapidly and is confronted by methodological challenges common to other areas of e-health including attrition and assessment reactivity and in the design of control conditions.

**Methods/design:**

The study aim is to evaluate the effectiveness of a brief online intervention, employing a randomized controlled trial (RCT) design that takes account of baseline assessment reactivity, and other possible effects of the research process. Outcomes will be evaluated after 3 months both among student populations as a whole including for a randomized no contact control group and among those who are risky drinkers randomized to brief assessment and feedback (routine practice) or to brief assessment only. A three-arm parallel groups trial will also allow exploration of the magnitude of the feedback and assessment component effects. The trial will be undertaken simultaneously in 2 universities randomizing approximately 15,300 students who will all be blinded to trial participation. All participants will be offered routine practice intervention at the end of the study.

**Discussion:**

This trial informs the development of routine service delivery in Swedish universities and more broadly contributes a new approach to the study of the effectiveness of online interventions in student populations, with relevance to behaviors other than alcohol consumption. The use of blinding and deception in this study raise ethical issues that warrant further attention.

**Trial registration:**

ISRCTN28328154

## Background

Alcohol causes huge problems, both for population health and for society more broadly. It is responsible for approximately 4% of the global burden of disease, similar to tobacco, with a greater impact in high-income countries and among men, for example accounting for 11% of all male deaths in WHO European Region in 2004 [1]. Population-level interventions that seek to influence the price, availability and cultural acceptability of hazardous and harmful drinking may be complemented by individual-level brief interventions delivered in health systems and elsewhere [2]. Brief interventions are typically offered opportunistically by non-specialists in routine contacts with patients attending healthcare services for other reasons and take only a few minutes to deliver [2,3].

Evidence for the effectiveness of brief interventions is based on randomized controlled trials and systematic reviews, which have consistently identified small effects on drinking behavior and related problems [4-6]. Although large-scale implementation programs are relatively recent, there have been longstanding difficulties in persuading generic health and welfare practitioners to embrace this work in routine practice [7]. The widespread use of computers and the internet offer other ways to reach large numbers of hazardous and harmful drinkers which overcome implementation problems due to practitioner reluctance to discuss drinking [7]. It may also be cheaper to implement online interventions and more acceptable to those targeted, though these features will not be important to public health unless interventions can also be demonstrated to be effective [8,9].

The research literature in this area is at an early stage of development but is evolving quickly. A number of recent systematic reviews provide preliminary evidence of effectiveness for a range of computerized interventions [10,11]. However, there are also examples of apparently well designed interventions (for example, [12]) not being found to be effective [13]. This highly naturalistic study was undertaken in a web browser population, and interpretation is complicated by the many unresolved methodological problems impeding progress in the evaluation of the effectiveness of online interventions [14]. Careful selection of study populations has been successfully used to demonstrate effectiveness in general population samples [15,16].

University student populations are very prominent in the existing literature, having been relatively extensively studied compared to non-students [11]. Heavy drinking among university students is a seemingly unremarkable and age-old phenomenon that is now globalized [17]. Given the well established role of heavy drinking in student cultures and the extent of internet use among students it is perhaps unsurprising that trials of internet interventions to promote safer drinking have been undertaken [18-20]. There are now effectiveness reviews of normative feedback interventions delivered in various ways among students [21] and of computerized interventions for this population [22].

Most previous student studies have required participants to attend laboratory or other controlled settings, rather than allowing access to interventions using their own computers [10,11,23]. Few of the published studies to date have described projects that have made comprehensive use of electronic media, by recruiting large numbers of participants via email, or allowed participants to engage with interventions naturalistically, when, where and how preferred by the participants themselves. Thus, most of the existing research has been undertaken in relatively artificial efficacy conditions, not closely resembling how interventions found to be effective would be routinely delivered [23].

The key exception to this is the research program on electronic screening and brief intervention (e-SBI) by Kypri and colleagues in Australia and New Zealand. Following earlier studies which recruited participants in student healthcare services [24-26], THRIVE was a large-scale effectiveness trial which invited 13,000 students to participate and subsequently randomized 2,435 risky drinkers to intervention or control conditions, with 2,050 providing follow-up data after either 1 or 6 months or both [27]. After 1 month there was a 17% reduction in alcohol consumption in the assessment and feedback group compared to a non-intervention assessment-only group. This had attenuated to an 11% difference after 6 months [27]. Currently under way in New Zealand are the first multisite large-scale effectiveness trials [8]. There remain many important knowledge gaps concerning the effectiveness of online interventions, including basic questions such as whether effectiveness is established and what effect sizes may be expected, under what conditions, for which populations and with which specific content (for example is feedback required, and if so should it be normative), as well as for different delivery models and across cultures.

Like their peers in other countries Swedish students also drink heavily. One recent study at Linköping University found that heavy episodic (or binge) drinking was normative, being reported by majorities of both sexes and almost three-quarters of all males [28]. The e-SBI model originally developed by the Lifestyle Intervention Research group at Linköping University was originally conceived within an effectiveness framework [29]. It is based upon an initial email to students from the student healthcare service, providing a link to a website for assessment and feedback. The core e-SBI content involves feedback on recommended limits of alcohol consumption and normative comparisons of drinking with Swedish students of the same age and sex. Previous research by this group has shown that this e-SBI model is a feasible way of reaching large numbers of students in ways permitting the conduct of effectiveness trials to evaluate detailed intervention content [29]. The first trial of this intervention found no differences between brief and more extensive normative feedback content though attrition problematically reduced available sample size [30]. Building upon the initial trial we undertook a further study as an unusually large pilot study with outcome data provided by 2,400 students to prepare for the trial described here. A key aim was to improve study retention and the implications of this pilot work for preparation and design of the present study are described in detail in the Methods section (a report is also being prepared for publication).

Among the issues that have presented difficulties in developing this area of research are uncertainties about the most appropriate control groups, due largely to overlap and similarities between feedback and assessment content [31]. Alcohol researchers have long been interested in the possibility that assessment or screening of alcohol consumption per se can reduce drinking [4,32,33]. It has not been unusual to observe reductions in drinking in non-intervention control groups of the order of 20% at later follow-ups [34,35]. These uncertainties have been made explicit by randomized controlled trials demonstrating apparent effects of assessment procedures, including when undertaken online [36] and when limited to screening alone [37]. In the latter case, pen and paper completion of the Alcohol Use Disorders Identification Test (AUDIT), a ten-item alcohol screening questionnaire [38], alone led to self-reported reduced drinking. While this could have been due to the specific effects of answering questions, it could also have been a Hawthorne effect in response to having one’s drinking studied [39], which this group may have inferred while the control group could not have done [37]. This entire literature is necessarily based upon self-reported drinking outcomes. Self-reports have been found to be reliable in alcohol treatment contexts [40] but have been little studied in brief intervention study contexts [41]. Assessment effects have also been conceptualized and studied in different ways in a range of disciplines and fields of research, and these have identified effects upon objectively ascertained outcomes in randomized trials [42-44].

In a recent systematic review of existing trials of randomized evaluations of assessment reactivity in brief intervention studies, effects were found to be of a somewhat smaller magnitude than typical brief intervention effects, hovering around the threshold for statistical significance, and being within the lower end of the confidence intervals for meta analytic estimates of effects [45]. When attention was restricted to university student populations, however, stronger effects were apparent, similar in magnitude to those of brief interventions themselves [45]. If simply by answering questions on one’s drinking, however, does subsequently lead to reduced drinking, large-scale implementation of simple screening surveys as interventions among university students might have a considerable public health potential [29]. This suggests also a need to demonstrate that more elaborate online interventions provide additional effects that are also acceptable to those targeted as well more cost effective than less elaborate interventions. There are as yet sparse data available on costs and cost effectiveness [46].

Making unbiased comparisons to guide decision making about alternative courses of action is the fundamental business of trials and assessment effects may introduce bias in studies of behavior change in ways that are not widely appreciated [47]. Better understanding the effects of assessment per se on drinking behavior should inform thinking both about intervention and control content. Other aspects of taking part in trials, apart from assessment reactivity, may also influence both research participation dynamics and the behaviors being studied and this possibility warrants dedicated studies [48]. For example, precisely what we expect participants to do in trials may well have implications for retention [49].

The overall aim here is to evaluate the effectiveness of e-SBI, employing an RCT design that takes account of baseline assessment reactivity and other possible effects of the research process [48]. Alcohol trials without any form of baseline assessment are rare and this situation hampers evaluation of the true effects of brief alcohol interventions whose content includes assessment [33,45]. Even more rare are studies that eschew typical trial recruitment processes due to concerns about interference with study aims, though they do exist (for example, [50]) and such Zelen designs [51] have been widely used in other areas [52]. The present study design will allow exploration of the magnitude of the feedback and assessment component effects, and is specifically designed to constrain possible effects of research participation on the control group, in testing e-SBI effectiveness.

## Methods/design

### Design

This is a three-arm parallel groups trial in which routine provision of e-SBI (group 1) is compared with assessment-only (group 2) and no contact control (group 3) study conditions. Groups 1 and 2 will complete identical assessments, the sole difference between them being that group 1 will receive normative feedback as usual whereas group 2 will not. Group 3 will only be contacted after 3 months, at which time both groups 1 and 2 also complete outcome data collection.

### Hypotheses

There are four main hypotheses, as follows:1) drinking in groups 1 and 3 will differ, with group 1 drinking less, providing a test of the effects of universal e-SBI provision in an unselected population of university students; (2) drinking in groups 2 and 3 will differ, with group 2 drinking less, providing a test of the effects of assessment-only in an unselected population of university students; (3) drinking in groups 1 and 2 will differ, with group 1 drinking less, providing a test of the effects of adding feedback to assessment-only among those who were risky drinkers participating at study entry; (4) drinking in groups 1 and 2 will differ, with group 1 drinking less, providing a test of the effects of adding feedback to assessment-only in an unselected population of university students.

Three hypotheses concern possible effects in unselected populations, that is, without reference either to drinking behavior or to earlier study participation. It is further hypothesized that these effects will be present among those whose drinking is determined to be potentially hazardous, that is, excluding non-drinkers and very infrequent drinkers (see Outcomes evaluation).

### Participants and setting

The study will be performed simultaneously at two different universities in Sweden, one in the northern part of Sweden, Luleå, and one in the southern part, Linköping. These institutions have been selected on the basis of previously conducted research involving the local student healthcare services who are responsible for alcohol interventions [29,30]. All students at both universities during the autumn 2011 term (that is, in terms 1, 3 and 5) will be included and all will be offered routine e-SBI provision during this term at the end of the study in addition to brief lifestyle feedback provided by the study (see below). Students in a single year group at one of the universities participated in a pilot study a year earlier (see below).

**Figure 1 F1:**
[figure not shown]
Flowchart for the Amadeus-1 trial.

### Blinding

Groups 1 and 2 are unaware that they are participating in a research study when they respond to the initial emails. Both groups are given to understand that these emails are provided as routine practice by the student healthcare centers to encourage students to consider their drinking. Thus, all three groups are unaware they are participating in an intervention study and that they have been randomized. Subsequently at follow-up, no explanation of the true nature of the study is given to students. Instead they are invited to participate in a seemingly unrelated cross-sectional lifestyle survey without any particular focus on drinking behavior (see Attrition). As all study procedures are automated, the research team has no direct contact with study participants. The use of blinding and deception in this trial raises ethical issues (see Discussion). The study was approved by the Regional Ethical Committee in Linköping, Sweden (number: 2010/291-31 on 12 October 2010).

### Sample size

The marginal costs involved in increasing the numbers to whom e-SBIs are delivered are negligible. Therefore even very small effects are likely also to be cost effective above the basic threshold cost involved in providing the service. These observations also apply to undertaking research to evaluate effectiveness and suggest that sample size should be as large as possible to detect very small effects. The pilot study indicated that any between-group differences are likely to be very small and it is a moot point as to whether this study should be even larger. Our power calculation assumed no difference between the 2 universities, and a follow-up rate of 50% (see Attrition below; 7,650 of a study population of approximately 15,300). For 3 groups of 2,550 this yields approximately 90% statistical power to detect an effect size of 0.09 standard deviations between any 2 contiguous pairs (group 1 vs group 2 or group 2 vs group 3) or 0.18 between group 1 and group 3. Alternatively we have in excess of 80% power to detect effects of 0.08 and 0.16 standard deviations, respectively.

This was only partially successful. Participation rates in ‘follow-up’ were slightly higher than at baseline (approximately 41% compared to 37%) in the two groups randomized to earlier contact. This comprised both the involvement of some who had not previously participated as well as attrition among some of those who had. While this measure had restricted the reduction in follow-up seen previously, it introduced a new problem; differential participation by group 3 (approximately 52%) comprised the equivalence of the three groups. By virtue of randomization, there was a strong basis for inferring that this could only have been caused by the earlier involvement with the study. The earlier invitation to participate in the alcohol e-SBI was not sufficiently different from the later alcohol survey. To rectify this, we decided for the main trial to abbreviate the alcohol outcome measures and conceal them within a lifestyle questionnaire in the follow-up study. It was reasoned that we had simply not gone far enough with our earlier attempt. Note that this extends blinding to a specific focus on alcohol at the point of outcome data collection. We will also add a third reminder at follow-up with the option of completing three items in the body of the email (as well as the hyperlink).

### Outcomes evaluation

Intention-to-treat analyses are primarily used in clinical trials to address problems with lack of compliance with allocated interventions [54,55]. In the present context the intervention comprises an automated email providing a means of accessing a website in an unselected population in which the prevalence of hazardous and harmful drinking is elevated. Lack of take-up of intervention is arguably more fundamentally a matter of reach rather than of effectiveness here, as there are not noteworthy costs associated with lack of take-up, though this situation does complicate evaluation of effectiveness and it is recommended that an attempt is made to account for all randomized participants [55]. The intervention could be defined more narrowly as delivered to those who access the website, with the email merely being the means of recruitment. Even if this definition is applied, the intervention will still be accessed by students whose drinking is not risky and who would thus not be deemed to merit individual targeting for intervention. More narrowly still, outcome evaluation could be restricted to those whose drinking is found to be risky. The overarching problem is that a greater number of people are randomized than would be targeted for intervention. Consideration of outcomes evaluation needs to take account of these issues.

By necessity, inferences involving group 3 can only be drawn in entirely unselected populations, as there are no baseline data with which one might construct subgroups randomized or otherwise for comparative purposes. Hence the form of hypotheses 1 and 2, which should be noted as highly conservative approaches to outcome evaluation as they will unavoidably include data that will bias the findings towards the null (both from non-participants at baseline and those who are not risky drinkers). To address this problem, analyses shall also be undertaken which exclude those determined in follow-up data to be unlikely to have been hazardous drinkers at study entry. Specifically non-drinkers and very infrequent drinkers (reporting never drinking or monthly or less frequently to AUDIT-C item 1; see below) will be excluded. This is also somewhat conservative to the extent that intervention effects may lead participants to drink rarely or not all but this does help with the problem previously described.

Hypotheses 3 and 4 concern only groups 1 and 2 and provide alternative ways of evaluating the specific effects of feedback. Hypothesis 3 is preferred as it addresses this question among the most relevant subpopulation of risky drinkers exposed to intervention who also later participated in follow-up and this will be the primary analysis for this question. It is acknowledged that the departure from intention-to-treat (ITT) implies a risk of bias. It is also judged that methods such as complier-average causal effect analysis are inappropriate due to the unusual study context. This reasoning for preferring a per protocol analysis over an intention-to-treat one has previously been applied in online alcohol trials [9].

### Outcome measures

Three items within the 15-item survey instrument are dedicated to assessment of drinking, alongside questions on smoking, diet and physical activity and sociodemographic characteristics. These items are the three questions of the AUDIT-C [56]. The two primary outcomes are AUDIT-C scores and the proportions of risky drinkers (according to the Swedish definition [57]). The three secondary outcomes are the component items of the AUDIT-C; number of heavy episodic drinking episodes per month, frequency of drinking and typical quantity consumed. The psychometric properties of these data when administered online have been found to be reliable in similar student populations [56,58].

### Data analyses

Intention-to-treat analyses in relation to hypotheses 1, 2 and 4 will be undertaken among all those providing follow-up data without any imputation for missing data. The only additional analyses here will consider how informative are patterns of response to reminders in relation to those not participating at follow-up and no attempt will be made to account for the randomized populations as a whole [55]. The per-protocol analysis for hypothesis 3 will be undertaken among all those in groups 1 and 2 who are risky drinkers at baseline who participate in follow-up. We will also include baseline measures of risk as covariates and examine patterns of attrition in these two groups and their possible impact on findings. We will undertake exploratory analyses of possible effect modification by university, term, faculty, age and gender. Effect sizes will be calculated as standardized mean differences or as ratio measures of effect. Student t tests and *χ*^2^ tests will be used supplemented by regression-based analyses as needed. All analyses will conform to a prespecified plan with data transformations appropriate for skewed data to be determined. There will be no interim analyses or stopping rules.

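### The analyses of hypotheses 1, 2 and 4 compare responders only, are labelled intention-to-treat and rule out accounting for everyone randomized, although half are expected not to respond and pilot response depended on allocation

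*Protocol article*

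**What the plan says.** The Data analyses section describes the analyses of hypotheses 1, 2 and 4 as intention-to-treat and says they are "undertaken among all those providing follow-up data without any imputation for missing data". On non-response it continues: "The only additional analyses here will consider how informative are patterns of response to reminders in relation to those not participating at follow-up", and then "no attempt will be made to account for the randomized populations as a whole". How the reminder analysis will be done, and whether it will be done by arm or change any estimate, is not stated.

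The Outcomes evaluation section cites the same reference when it notes that "it is recommended that an attempt is made to account for all randomized participants".

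The Sample size section assumes "a follow-up rate of 50% (see Attrition below; 7,650 of a study population of approximately 15,300". It states: "For 3 groups of 2,550 this yields approximately 90% statistical power to detect an effect size of 0.09 standard deviations" between contiguous groups, or 0.18 SD between groups 1 and 3. It also gives more than 80% power for 0.08 and 0.16 SD.

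The Attrition section reports pilot follow-up participation of about 41% in groups 1 and 2 combined, and says that "differential participation by group 3 (approximately 52%) comprised the equivalence of the three groups" (the verb is evidently meant as compromised). It infers from randomization that only the earlier involvement with the study could have caused this. In response, the main trial hides shortened alcohol items in a lifestyle survey and adds a third reminder with items in the email itself.

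**The concern.** An analysis of roughly half of those randomized keeps the protection of randomization only if non-response does not distort the contrast between arms. The protocol's own pilot gives reason to doubt this for hypotheses 1 and 2, because being contacted earlier changed how many people answered. The sample size allows for the 50% loss in precision but nothing in the plan allows for it in bias.

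The effects sought are very small, so modest selection matters. If heavier drinkers answer less readily, the lower response in groups 1 and 2 makes those groups look lighter and mimics a benefit. If heavier drinkers answer more readily, it hides one. The intention-to-treat label would lead readers to think this had been dealt with.

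The point is not a detail left to an unseen analysis plan. The protocol states which additional analyses there will be and rules out the rest.

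**Working it through.** **Inputs.** About 15,300 randomized 1:1:1, so 5,100 per group; 50% follow-up, so 2,550 per group; targets as in the Sample size section; pilot participation 41% (groups 1 and 2) and 52% (group 3), hence loss of 59% and 48%. Two-sided alpha of 0.05 is an assumption, since the article does not state it. The documents give no difference in drinking between responders and non-responders, so that gap is varied.

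**1. The stated power.** The standard error is √(2/2,550) = 0.0280 SD. For 0.09 SD: Φ(0.09/0.0280 − 1.96) = 89.5%. For 0.08 SD: 81.5%. Both match the protocol, so the sample size is not in error.

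**2. Unequal response, same gap in every arm.** Let g be the responder mean minus the non-responder mean, in SD, and r the response rate. The responder mean is μ + (1 − r)g. With no true effect, the responder difference between a contacted group and group 3 at pilot rates is (0.59 − 0.48)g = 0.11g. With 5,100 × 0.41 = 2,091 and 5,100 × 0.52 = 2,652 responders, the standard error is √(1/2,091 + 1/2,652) = 0.0292. The type I error is Φ(b/SE − 1.96) + Φ(−b/SE − 1.96), where b is the bias.

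| Assumed g (SD) | Bias at 41% vs 52% | Share of 0.09 SD | Type I error | Bias at 48% vs 52% | Type I error |
|---|---|---|---|---|---|
| 0.1 | 0.011 | 12% | 6.6% | 0.004 | 5.2% |
| 0.2 | 0.022 | 24% | 11.7% | 0.008 | 5.9% |
| 0.3 | 0.033 | 37% | 20.4% | 0.012 | 7.1% |
| 0.5 | 0.055 | 61% | 46.8% | 0.020 | 11.0% |

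Under this model a bias of the full 0.09 SD needs g = 0.09/0.11 = 0.82 SD. Against the 0.18 SD target of hypothesis 1, the largest bias shown is 0.055/0.18 = 31%.

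**3. Equal response, different gaps.** At 50% in both arms the bias is 0.5 × (difference in g between arms). A difference of 0.10 SD gives 0.05 SD and a type I error of 43%; a difference of 0.18 SD gives 0.09 SD. Equal response rates are therefore reassuring but not sufficient. This case is the relevant one for hypothesis 4.

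**4. Worst case by trimming.** Let q = (r_high − r_low)/r_high. If the excess responders are exactly the most extreme drinkers and the outcome is normal, the bias is φ(z)/(1 − q), with z the (1 − q) normal quantile.
- 49% vs 51%: q = 0.0392, z = 1.760, bound 0.0848/0.9608 = 0.09 SD.
- 48% vs 52%: q = 0.0769, bound 0.16 SD.
- 41% vs 52%: q = 0.2115, z = 0.801, bound 0.2894/0.7885 = 0.37 SD.

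These are limits, not expected biases. The protocol itself anticipates skewed data, so the normal form is an approximation.

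**5. What non-responders can do to a finding.** At 50% response the difference in the whole randomized population is 0.5 × (responder difference) + 0.5 × (non-responder difference). An observed 0.09 SD becomes 0.045 SD if non-responders show no difference, and zero if theirs is −0.09 SD.

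**The case against.** The strongest defence is that the protocol met this problem by design. It diagnosed the pilot imbalance as the follow-up looking too much like the earlier alcohol contact, and changed the follow-up accordingly. It names constraining differential attrition as a main innovation. That bears on how likely the problem is, and pilot rates should not be carried forward as a forecast. It does not replace an analysis: the pilot's own separation of follow-up from intervention was only partly successful, and nothing is planned should the redesign fall short.

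Several stronger readings are tempting but not supported:

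- **That non-response is ignored.** A reminder-pattern analysis is planned, and nothing stops it being done by arm. It is too vague to rely on, which is a different criticism. Attrition patterns in groups 1 and 2 are also to be examined, in the context of hypothesis 3.
- **That 41% and 52% were lost.** These are participation rates; the contacted groups lost more, 59% against 48%.
- **That the pilot undermines hypothesis 4.** It gives one combined figure for groups 1 and 2 and reports no imbalance between them.
- **That bias of pilot size exceeds the target several times over.** The pilot shows how many answered, not how they differed in drinking. The 0.37 SD bound needs the most extreme selection possible, and for hypothesis 1 it is about twice the 0.18 SD target.
- **That the protocol contradicts itself.** It reports the recommendation, notes that the design complicates matters, and later declines it openly. That is a declared departure, not an inconsistency.

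**Conclusion.** The concern holds in a limited form. A responder-only comparison is called intention-to-treat, and further accounting for those randomized is expressly excluded, with 50% non-response expected. For hypotheses 1 and 2 the protocol's own evidence is that allocation can alter response. For hypothesis 4 only the label and the size of the loss are at issue.

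The plausible distortion at pilot response rates is 0.011 to 0.055 SD, with type I error of about 7% to 47%. It is much smaller if the redesign brings response to 48% against 52%. This range rests on the assumed gap of 0.1 to 0.5 SD, the same in all arms, and on two-sided 0.05. The trimming bounds, 0.09 SD at 49% vs 51% and 0.37 SD at 41% vs 52%, mark what the data could not exclude. None of this shows that the trial will be biased. It shows that, as planned, a positive or null result on hypothesis 1 or 2 could not readily be told apart from an effect of non-response. The remedy is cheap enough that it should be made.

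**What to change.** The Trial status section says that no follow-up invitations had gone out at submission, so the change could be made before any outcome was seen.

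1. Call the analyses of hypotheses 1, 2 and 4 responder (complete-case) analyses by allocated group, and delete the clause "no attempt will be made to account for the randomized populations as a whole".
2. Report follow-up response by arm before any outcome comparison.
3. Carry out the reminder-wave analysis by arm, and say how it will inform the interpretation.
4. Prespecify an arm-specific delta (tipping-point) analysis for non-responders, with the range justified in advance, and report it beside the main estimates.
5. For hypotheses 1 and 2, add trimming bounds if response differs between arms.

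Multiple imputation is not essential. Group 3 has no baseline data, and the register information described is mainly university and year, so imputation would recover little for the contrasts with group 3.

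The cost is a few extra analyses on data already held, and more cautiously worded conclusions.
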